### Comparison Arm

Women in the comparison arm are directed to an alternate version of the I-DECIDE website that represents the usual resources currently available through most domestic violence organisations. The comparison website includes the study measures as well as a standard “emergency safety plan” and links to national support service websites. It also includes static information on a healthy relationship, without any interactive elements.

### Safety procedures

Safety information is provided to all participants regarding the safe use of computers and the internet. Additionally, I-DECIDE is designed with a ‘quick escape’ bar that allows immediate exit and log out from I-DECIDE and returns the user to a generic website such as Google. A new browser window opens up with another generic website so that if a perpetrator forces a woman to click ‘Back’ on her browser it will not return to I-DECIDE. All automated emails sent to participants have the subject header “Women’s Health Study” and come from a specific email address ([contact]) that is separate to the regular project email address.

Should a woman contact a member of the research team because she is upset due to her participation in I-DECIDE, the researchers will refer to the study distress protocol in their response. The protocol includes exploring with the individual whether they have someone they can talk to who will understand and be supportive. The research team member will discuss with the participant where they might seek support, including the agencies detailed on the resource list provided to all participants. An independent Data Monitoring Committee (DMC) has been established in order to ensure that the trial is conducted appropriately. The DMC is scheduled to meet following major trial events and data collection milestones and at least annually. The DMC is composed of experts in randomised controlled trials and intimate partner violence. They will ensure that trial participants are protected, and will monitor the overall conduct of the trial.

### Outcomes

The primary outcomes, measures and hypotheses of the I-DECIDE trial are shown in Table 1 and the secondary outcomes in Table 2. Costs of managing and operating the website will be calculated from study records. Women’s time costs will be measured via recorded website analytics (time spent on website) and valued at the average Australian wage rate. Women’s use of services will be measured by responses to an adapted version of an instrument developed by Watson et al. [29] and valued using existing unit cost estimates. All costs will be presented in 2015 Australian dollars. Cost effectiveness will be assessed after 12 months as the additional cost per point change in self-efficacy and CESD-R. Harms and benefits of the study will also be explored using an adapted version of the COST Questionnaire [30].

### Data analysis

Characteristics of participants in each of the two study arms will be summarised using means and standard deviations or percentiles for continuous data, and frequencies and percentages for categorical data. Characteristics of participants in the two study arms will be compared at baseline to ensure that the randomisation was effective. Subsequent analyses will adjust for any baseline imbalances between groups strongly associated with the outcomes. Mixed effects linear regression will be used to compare scores between the two study groups on continuous outcomes [31]. Any count data which is skewed will be analysed using a Poisson model [32]. All regression models will adjust for baseline outcome measures and for any baseline imbalances strongly associated with the outcomes. Analyses will also take into account repeated measures over time (i.e. study group will be fitted as a fixed effect, and change over time within groups as random effects). A two-tailed alpha level of .05 will be used throughout analyses. Intention to treat and completed case analyses will be performed. Missing data will be assessed for patterns, including whether the data is missing completely at random (MCAR), missing at random (MAR), or missing not at random (MNAR) [33]. This will include analyses to determine whether particular participant characteristics or outcomes are associated with missing data, and whether any missing data patterns found are similar or different between intervention and comparison groups. Either multiple imputation or likelihood-based analysis will be used to account for missing data, depending on the nature of the missing data, and which assumptions are met [33].

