Outcome	Measure	Description & purpose	Hypothesis
Actions for safety and wellbeing	weave service use & activities questionnaire (modified)^a^	These questions drawn from the *weave* study [11] ask women what activities or services she has used over the past 6 months. If she answers ‘yes’ to any items, a second question drops down asking whether it was helpful (yes/no).	A higher mean number of actions for safety and wellbeing that are helpful than the comparison group, at 6 months post-baseline.
	Self-care activities questionnaire^1^	These questions are a modified list of self-care activities derived from the *Diamond* study on depression [36]. Women are asked if they have started doing, or increased the frequency, of any of the listed self-care activities. If she answers ‘yes’ to any items, a second question drops down asking whether it was helpful (yes/no).	
Fear of partner	Visual Analogue scale 0-100	The participant will be asked to rate their current level of fear of their partner or ex-partner, on a sliding scale from 0 (not at all afraid) to 10 (very afraid).	A lower mean fearfulness score than the comparison group, as measured on a visual analogue scale of current level of fear of partner (0–100), at 12 months post-baseline

^a^These questions were developed for the purposes of this study

**Table 3 Tab3:** Mediators of the outcomes

Measure	Outcome	Description & purpose
Perceived support - visual analogue scale^a^	Perceived support (website)	The participant will be asked to rate how supported they feel by the website on a sliding scale from 0 (completely unsupported) to 10 (completely supported).
Contemplation Ladder, modified version^a^	Awareness	Women will indicate their position on a modified version of the Contemplation Ladder [37], a tool originally developed to measure readiness to cease smoking. The ladder is designed to measure awareness of abuse from 0–10 based on how ready the woman is to make positive changes to her situation.

^a^These questions were developed for the purposes of this study

**Table 4 Tab4:** Moderators of the outcomes

Measure	Outcome	Description & purpose
*Diamond* life event questionnaire	External events	This questionnaire was taken from the *Diamond* longitudinal depression study [36]. Questions ask whether a woman has experienced any of 13 significant life events over the last 12 months, and if so, whether it had a positive or negative impact.

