### Number of participants required

A final sample size of at least 141 women in each of the two groups will be required to detect differences of a third of a standard deviation between group means on the primary outcomes (see Table 1) at 6 and 12 months, with at least 80 % power (alpha 5 %, 2-sided test). Attrition of up to 30 % has been found in previous studies with this population in Australia [11] and the US [24]. Allowing for an attrition rate of 30 % by the 12 month follow-up time point, at least 404 eligible women will need to be recruited to the baseline phase of the trial (202 women in each group).

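### Skewed counts are assigned to a Poisson model with no stated provision for overdispersion; if helpful actions are overdispersed, the 5% test could reject too often

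*Protocol article*

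**What the plan says.** In the protocol article, the Data analysis section assigns continuous outcomes to mixed effects linear regression and then adds: "Any count data which is skewed will be analysed using a Poisson model". No check of the variance against the mean is named, and no robust, quasi-Poisson or negative binomial alternative.

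Three later sentences of the same section bear on the count model:
- On covariates: "All regression models will adjust for baseline outcome measures and for any baseline imbalances strongly associated with the outcomes".
- On repeated measures, the section explains that "study group will be fitted as a fixed effect, and change over time within groups as random effects".
- On the significance level: "A two-tailed alpha level of .05 will be used throughout analyses".

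Table 2 (under Aims of I-DECIDE) defines the outcome. The hypothesis is "A higher mean number of actions for safety and wellbeing that are helpful than the comparison group, at 6 months post-baseline". The count comes from lists of services, activities and self-care items: "If she answers ‘yes’ to any items, a second question drops down asking whether it was helpful (yes/no"). It is therefore a sum of yes/no items and cannot exceed the number of items, which is not given.

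**The concern.** Skewness does not decide whether a Poisson analysis is valid. A correctly specified Poisson variable is itself skewed when its mean is small, and a skewed count can have a variance below, at or above its mean. What matters for the standard error is the ratio of variance to mean, φ. If φ exceeds 1, the model-based standard error is too small by a factor of √φ.

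There is reason to expect φ above 1 here. A woman who took no action scores zero on every helpfulness item. Women also differ in whether they intend to stay, intend to leave or have already left, and in whether they have children. All of this makes items within a woman move together.

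At stake is a secondary outcome that the Aims section treats as a hypothesised consequence of the internal changes the website targets. A chance excess of helpful actions could be reported as a finding, with an interval that is too narrow.

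**Working it through.** **The plan's own figures.** The article gives no figure for the count outcome. The related figures are the two-sided 5% level and the sample size, which was set for the primary outcomes at an effect of 1/3 SD: "A final sample size of at least 141 women in each of the two groups will be required". The sample size reproduces: 2(1.96 + 0.84)²/(1/3)² ≈ 141.3 per arm, against 141 stated; 141/0.70 = 201.4, hence 202 per arm and 404 in all. I use 141 per arm below.

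**Plain Poisson test, model-based standard error.** With true variance = φ × mean, the Wald statistic under the null has standard deviation √φ instead of 1, so

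type I error = 2[1 − Φ(1.96/√φ)].

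In large samples neither the mean nor the sample size enters. φ is my assumption:

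| φ | 1.96/√φ | Type I error |
|---|---|---|
| 1.0 | 1.96 | 5.0% |
| 1.2 | 1.79 | 7.4% |
| 1.5 | 1.60 | 11.0% |
| 2.0 | 1.39 | 16.6% |
| 3.0 | 1.13 | 25.8% |

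Simulation agrees (negative binomial counts, means 3 and 5, 141 per arm, 4,000 trials per setting): 11–12% at φ = 1.5, 17% at 2 and 25–26% at 3.

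**A bounded sum of yes/no items.** For k items, each with probability p and inter-item correlation ρ, φ = (1 − p)[1 + (k − 1)ρ]. I assume k = 20, with 4,000 simulated trials per setting:

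| p | ρ | φ | Poisson, model-based | Poisson, robust |
|---|---|---|---|---|
| 0.15 | 0 | 0.85 | 3.3% | 5.2% |
| 0.25 | 0 | 0.75 | 2.4% | 5.2% |
| 0.15 | 0.02 | 1.17 | 6.5% | 4.8% |
| 0.25 | 0.05 | 1.46 | 10.1% | 4.5% |
| 0.15 | 0.05 | 1.66 | 12.9% | 5.1% |
| 0.25 | 0.10 | 2.18 | 18.2% | 5.3% |
| 0.15 | 0.10 | 2.47 | 21.9% | 5.4% |

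Independent items give an underdispersed count and a conservative test. With p = 0.25, φ passes 1 once ρ exceeds (1/0.75 − 1)/19 ≈ 0.018, so a small correlation is enough. In the same setting (k = 20, p = 0.25), independent items had skewness of about 0.25, while ρ of 0.05 to 0.20 gave skewness 0.5–0.85 and φ 1.5–3.6. Under these assumptions, a skewness trigger tends to pick out the overdispersed case.

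**Adjusting for the baseline count.** With k = 20, p = 0.25, a latent baseline to follow-up correlation of 0.5 and 1,500 trials per setting, the model-based test rejected in 8.5%, 16.2% and 24.7% of trials at ρ = 0.05, 0.10 and 0.20. At latent correlation 0.7 and ρ = 0.10 the rate was 13.9%. Adjustment lowers the excess but does not remove it. Robust standard errors kept these rates between about 4% and 6%.

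**Adding a woman-level random intercept.** On negative binomial data with mean 5 (600 trials per setting), rejection was 4.3%, 5.3% and 5.0% at φ = 1.5, 2 and 3, which is nominal.

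**The case against.** Four points can fairly be made for the plan.

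1. *No dispersion is given, and a bounded sum of yes/no items may be underdispersed.* This stands as a limit on what can be claimed. A reader might infer that the analysis will have a false-positive rate of 10% or more. The documents do not support that: they give no variance, and with independent items the rate is below 5%. Overdispersion is the likelier case given how the items arise, but it is not established.

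2. *The random-effects sentence may already deal with it.* A woman-level intercept in the Poisson model would restore about 5%, and the sentence is not limited to the linear models. But it speaks of change over time and is introduced to handle repeated measures, whereas the actions hypothesis is stated at 6 months only. If baseline enters as a covariate and only 6 months is modelled, each woman contributes one row and there is no repeated measure. The text does not settle which model is meant, so the protection cannot be relied on.

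3. *Helpful actions are not expressly assigned to Poisson.* True: the sentence applies only if the counts are skewed. That dependence on observed skewness is part of the problem.

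4. *A journal article leaves variance estimators to the analysis plan.* Silence would have been no finding. Here the article names a model and a criterion for using it, and the criterion does not address the assumption the model depends on.

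**Conclusion.** The point holds in conditional form. The article fixes a Poisson model for skewed counts, uses a criterion unrelated to the validity of its standard errors, and states no provision for overdispersion. If φ is 1.5 to 3, model-based standard errors are used and no woman-level random effect is fitted, the two-sided 5% test rejects a true null about 11% to 26% of the time, and somewhat less often after baseline adjustment. With nearly independent items it rejects about 2% to 3% of the time. The values of φ, k, p and ρ are assumptions, since the documents give none.

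The consequence is confined to count outcomes, chiefly one secondary outcome. A reader might infer that the trial's main conclusions are at risk. They are not: self-efficacy and depressive symptoms are continuous scores analysed by mixed linear regression.

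**What to change.** Replace the Poisson sentence with: *Count outcomes will be analysed by Poisson regression with robust standard errors (or negative binomial regression), adjusted for the baseline count, and reported as a rate ratio with 95% CI, whatever the observed skewness.* One of the two should be chosen before the data are seen. Also state whether the random-effects sentence applies to the count model.

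The cost is one sentence. The interval becomes wider when counts are overdispersed, as it should. If φ is 1, robust standard errors change almost nothing (simulated rejection 5.5–5.9%, against 5.2–5.6% with model-based errors). If the count is underdispersed, they bring the conservative 2–3% back to about 5%.

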### Aims of I-DECIDE

The primary aim of the I-DECIDE trial is to determine if an interactive web-based healthy relationship tool and safety decision aid compared to a non-interactive information only website results primarily in:Increased self-efficacyDecreased depressive symptoms

The secondary aims are to determine if the intervention results in:Increased helpful actions for safety and well beingDecreased fear of their partner and is cost effective.

The intervention website consists of self-reflection on behaviours from their partner, a danger assessment, messaging about their relationship and their safety, weighing up different priorities for their relationship and a tailored action plan). We hypothesise that the intervention will increase women’s perceived support and awareness of the abuse, which will increase their readiness for action with regard to their relationship and their self-efficacy and that these internal changes will lead to increases in safety and wellbeing actions and improvement in women’s depressive symptoms (see Tables 1, 2 and 3).

**Table 1 Tab1:** Primary outcome measures

Outcome	Measure	Description & purpose	Hypothesis
Self-efficacy	The General Self-Efficacy Scale	The scale assesses a general sense of perceived self-efficacy, aiming to predict coping ability and adaptation to stressful life events. The Scale has 10 questions with response choices on a 4-point scale: Not at all true/Hardly true/ Moderately true /Exactly true.	A higher mean self-efficacy score than the comparison group, by at least a third of a standard deviation, as measured by the General Self-Efficacy Scale [34], immediately after intervention completion and at 6 and 12 months post-baseline.
Depression	The Center for Epidemiologic Studies Depression Scale, Revised (CESD-R)	The Center for Epidemiologic Studies Depression Scale (CESD) is widely used in community samples. The 20 items in the CESD-R scale measure symptoms of depression in nine different groups as defined by the DSM-IV. Users are asked to rate the occurrence of symptoms ‘in the past week or so’ from 0 (Rarely or none of the time – less than one day) up to 4 (Nearly every day for two weeks)	A lower mean depression score than the comparison group, by at least a third of a standard deviation, as measured by The Center for Epidemiologic Studies Depression Scale, Revised (CESD-R) [35] at 6 and 12 months post-baseline.

**Table 2 Tab2:** Secondary outcome measures

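### The stated mixed model gives one group effect averaged over visits, whereas the primary hypotheses and the sample size concern differences at named visits

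*Protocol article*

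**What the plan says.** The analysis method is given in the protocol article under Data analysis: "Mixed effects linear regression will be used to compare scores between the two study groups on continuous outcomes". The text then says how repeated measures are handled and spells out the model terms: "study group will be fitted as a fixed effect, and change over time within groups as random effects". Further fixed terms come from the sentence before it: "All regression models will adjust for baseline outcome measures and for any baseline imbalances strongly associated with the outcomes". The article names no fixed effect of visit, no group-by-visit interaction and no contrast at a given visit.

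The hypotheses are tied to visits. Table 1, under Aims of I-DECIDE, expects a difference of at least a third of a standard deviation in self-efficacy "immediately after intervention completion and at 6 and 12 months post-baseline", and in CESD-R "at 6 and 12 months post-baseline". The abstract lists the same times. The section on the number of participants sizes the trial to "detect differences of a third of a standard deviation between group means on the primary outcomes" at 6 and 12 months, "with at least 80 % power (alpha 5 %, 2-sided test").

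**The concern.** A random effect describes how individuals scatter around a mean. It has expectation zero, so it cannot carry a systematic change over time, nor a group difference that is larger at one visit than at another. With change over time entered only as random effects, the treatment comparison rests on a single group coefficient, which is a weighted average of the visit-specific differences.

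For self-efficacy that average includes a measurement taken straight after use of the website, together with those at 6 and 12 months. A constant effect over that span is a strong assumption. The article's own account of mechanism is a sequence, in which internal changes come first and actions and depressive symptoms follow. An analyst who followed the text would obtain one number per outcome. Table 1 asks for three on self-efficacy and two on CESD-R.

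**Working it through.** **1. The plan's own figure.** Inputs from the section on the number of participants: difference 1/3 SD, two-sided alpha 5%, power 80%, attrition 30%.
- n per group = 2 × (1.960 + 0.842)² / (1/3)² = 141.3, which rounds up to 142. With 141 the power is 0.799, so the stated 141 is reproduced to rounding.
- 141 / 0.70 = 201.4, so 202 per group and 404 in total, as stated.

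This is a comparison of two means at one time point. The planned size therefore refers to a visit-specific difference, not to a pooled one.

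**2. Complete data.** With every visit observed and equal correlation between visits, the single group coefficient is the plain average of the visit differences, whatever the correlation. For two visits, as for CESD-R:
- true 0.50 and 0.17 SD: (0.50 + 0.17)/2 = 0.33. A large simulated fit (20,000 per arm) gave 0.33 from the stated model, and 0.50 and 0.16 once visit and group-by-visit were added.
- true 0.33 and 0 SD: 0.33/2 = 0.17. The simulated fit gave 0.18, against 0.34 and 0.02 with the interaction.
- true 0.33 and 0.33 SD: the simulated fits gave 0.34, against 0.34 and 0.33. The models agree.

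**3. Self-efficacy with dropout.** Assumptions, not from the protocol: 202 per arm at the immediate measurement; 15% lost by 6 months; correlation 0.5 between any two measurements; a random intercept only. The 30% lost by 12 months is the plan's figure.

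After baseline adjustment, residual variances are 0.75 and covariances 0.25. A woman with T post-baseline visits gives each visit the weight 1/(0.5 + 0.25T): 1.333 for one visit, 1 for two, 0.8 for three. The shares of women with one, two and three visits are 0.15, 0.15 and 0.70.
- Immediate: 0.15 × 1.333 + 0.15 × 1 + 0.70 × 0.8 = 0.91
- 6 months: 0.15 × 1 + 0.70 × 0.8 = 0.71
- 12 months: 0.70 × 0.8 = 0.56
- Sum: 2.18. The 12-month visit has 0.56/2.18 = 26% of the weight and the immediate one 42%.
- SE of the pooled effect = √(2/(202 × 2.18)) = 0.067 SD.

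| True effects (immediate, 6, 12 months) | Pooled effect | z | Power |
|---|---|---|---|
| 0.5, 0.15, 0 | (0.455 + 0.1065)/2.18 = 0.258 | 3.82 | 97% |
| 0, 0.1, 1/3 | (0.071 + 0.1867)/2.18 = 0.118 | 1.75 | 42% |
| 1/3 at all three | 0.333 | 4.95 | over 99% |

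For comparison, a single 12-month contrast with 141 per arm has SE √(2 × 0.75/141) = 0.103. At 1/3 SD, z = 3.23 and power is 0.898 at two-sided 0.05.

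For the first pattern, 100 simulated trials with a random slope added to the random intercept gave a mean estimate of 0.255 SD and 94% rejection, in line with the closed form given that few runs. A random slope can shift the weights, but it does not produce visit-specific differences.

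**The case against.** The strongest reply is that the parenthesis is shorthand. It explains how within-woman dependence is handled and is not a full list of fixed effects, since baseline covariates are named separately. A condensed article would normally leave visit coding, interactions and contrasts to the analysis plan, and nothing says that only a pooled estimate will be reported. Part of this stands: the intended model may well be sounder than the text, and it would be wrong to say that study group is the only fixed effect. But the article is not silent here. It spells out which term is fixed and places change over time among the random effects. That is a statement of the model, and it does not match Table 1.

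The second reply is that the harm depends on chosen patterns. This also stands. Table 1 expects at least a third of an SD at every named time. If the effect is a constant 1/3 SD, the stated model is unbiased and has over 99% power, more than any single-visit contrast. The 90% comparator is also for one test at 0.05. Bonferroni testing of three times would bring it to about 80%.

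A reader might also infer that the 97% rejection rate under effects of 0.5, 0.15 and 0 SD is a false-positive rate. It is not. The immediate and 6-month times are primary for self-efficacy, and the effects there are real in that scenario. The error would lie in reading the pooled 0.26 SD as a 12-month result, and the article does not say it will do so.

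**Conclusion.** The point holds as a mismatch between the stated model and the stated hypotheses. Followed as written, the model gives one time-averaged difference per outcome and cannot give the visit-specific differences in Table 1 or those on which the sample size rests. That conclusion follows from the terms named and needs no assumed effect size.

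The size of the consequence does depend on assumptions. It is nil for a constant effect. Under the two time-varying patterns above, the pooled estimate is about 0.26 SD where the 12-month effect is zero, and about 0.12 SD where it is 1/3 SD. In the second case power is about 42%, against about 90% for a single 12-month contrast. These figures assume 15% dropout by 6 months, correlation 0.5 and a random intercept, and they apply to self-efficacy. For CESD-R only the complete-data averages in step 2 were worked.

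The documents do not support going further and making 12 months the only primary contrast. The abstract, Table 1 and the sample size section do not single it out.

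**What to change.** Replace the parenthesis under Data analysis with the following: fixed effects for group, visit (categorical), group-by-visit and baseline score, with participant-level random effects or a within-woman covariance structure. State that the model-based group difference will be reported at each time point named in Table 1: immediately, 6 and 12 months for self-efficacy, and 6 and 12 months for CESD-R. Baseline-by-visit terms and an unstructured covariance are optional.

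The change needs no new data and does not alter the sample size, which is already calculated for one time point. The article gives the trial as still recruiting, with investigators blinded until after the 12-month analysis, so the wording can be settled before unblinding. The cost is a few more parameters, and lower power than the pooled estimate if the effect is in fact constant over time.
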